### Measured 4–8 weeks post-natal

*Maternal satisfaction*, assessed by questionnaire

Fetal and neonatal:

### Measured at time of birth

*Live birth* (yes/no);*Se*x (male/female)*5-min Apgar score* (median measurement, and proportion with score < 7)*Birthweight* (mean measurement in grams)*Birth injury* (severe bruising, nerve trauma, or fracture) (yes/no)*Arterial cord-gas results* (mean lactate or pH measurement, if pH then proportion < 7.0)

### Measured before hospital discharge

*Admission to neonatal intensive care unit*/special care baby unit (yes/no)*Need for respiratory support* or mechanical ventilation (yes/no) and duration (time in hours will be calculated at the end of the study, based on times recorded by the staff member (from time of starting to time of stopping intervention), mean duration)*Length of stay* (time in hours will be calculated at the end of the study, based on times recorded by the staff member (from time of admission to time of discharge from the neonatal intensive care unit (NICU)), mean duration) (also proportion of admissions > 4 h)*Infection* (either culture proven or clinically suspected with supporting laboratory evidence such as raised white blood cell count or C-reactive protein) (yes/no)*Seizures* (yes/no)*Neonatal encephalopathy*, (yes/no, and if moderate or severe, and if due to hypoxic ischemic encephalopathy)*Early neonatal death* (yes/no)

Hospital:
*Staff satisfaction*, assessed by questionnaire, measured annually at each participating hospital*Maternal length of stay*; (time in hours will be calculated at the end of the study, based on times recorded by the staff member (from time of admission to time of discharge from hospital), mean duration)*Neonatal length of stay*; (time in hours will be calculated at the end of the study, based on times recorded by the staff member (from time of admission to time of discharge from hospital), mean duration)*Pharmaceutical, equipment, and consumable costs*; health care utilisation costs; incremental cost-effectiveness ratio (ICER) for risk of caesarean section (see ‘Cost effectiveness analysis’ section)

*Participant timeline*: see Fig. 1.

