### Measured at time of induction of labour

For balloon catheter only:
Duration in situ (time in hours will be calculated at the end of the study, based on times recorded by the staff member (from time of placement to time of removal/falling out)Balloon catheter removed or fell out, measured by staff member when patient readmitted to hospitalEarly unplanned return to hospital (yes/no) and reason, collected by staff member when patient readmitted to hospitalFor PGs only:
Total number of doses given (compare median number between groups)For both methods:
Discomfort during placement (NPRS, from 0 (no pain) to 10 (worst possible pain)), asked by staff member to the patient using a pictorial of the pain scale, measured in the first few minutes after placementNeed for second method of cervical ripening (proportion of participants who need a second method, yes/no)Need for ARM (proportion of participants who need ARM, yes/no)Discomfort during ARM (NPRS, from 0 (no pain) to 10 (worst possible pain), asked by staff member to the patient using a pictorial of the pain scale, measured in the first few minutes after ARM

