### Measured at time of birth

Proportion of participants who had use of oxytocin infusion and at what cervical dilation it started (median score, from 0 to 10)Uterine hyperstimulation (yes/no)Proportion of participants who had use of epidural anaesthesia and at what cervical dilation it was placedClinical diagnosis of chorioamnionitis (yes/no)Proportion of participants who had a clinically significant antepartum haemorrhage after start of IOL – cause, timing, and if associated with abnormal CTGFetal blood sampling (lactate or pH) performed during labour (proportion of participants who had this done) and results (mean measurement)Mode of birth (proportion of participants who had spontaneous vaginal, assisted vaginal or caesarean section)Proportion of participants who had a vaginal birth within 24 h of start of IOLIf caesarean section, reason and at what cervical dilation (mean score, from 0 to 10)Proportion of participants who had failed IOL (defined for the purposes of this study as caesarean section performed at < 4 cm)Uterine rupture (yes/no)Non-cephalic presentation (yes/no)Cord prolapse (yes/no)Stillbirth (yes/no)

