### Statistical analysis

Baseline demographic and clinical characteristics will be described for each study group. Analyses will follow the principle of intention-to-treat; participants will be analysed according to the assigned intervention group at randomisation. Multivariable models will control for potentially confounding variables and include hospital site and parity. Binary endpoints will be analysed using logistic regression to estimate odds ratios for the intervention. Continuous outcomes will be modelled using generalised linear models to estimate any changes in outcomes between the two interventions. A *p* value of 0.05 will be considered as statistically significant. We recognise that there are a number of secondary outcomes; as they are secondary outcomes we will report *p* values without correction, which would be overly conservative. Missing data will not be imputed.

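### Some secondary outcomes exist only after a post-randomisation event, yet the general analysis rule would compare them between arms as if randomised

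*Protocol article*

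**What the plan says.** The secondary outcome lists in the protocol article contain several measures that have a value only if something happened after randomisation.

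- **Neonatal unit stay** (Measured before hospital discharge): "from time of admission to time of discharge from the neonatal intensive care unit (NICU)), mean duration) (also proportion of admissions" above a 4 h cut-off.
- **Respiratory support** (same list): a yes/no item, plus a duration taken "from time of starting to time of stopping intervention), mean duration".
- **Dilation at oxytocin start** (in the list Measured at time of birth), where the entry reads "Proportion of participants who had use of oxytocin infusion and at what cervical dilation it started (median score, from 0 to 10". The entry for epidural is built the same way but names no summary statistic.
- **Dilation at caesarean** (same list): a mean, in an entry that is explicitly conditional on a caesarean having been done.

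Most of these sit beside a partner defined for every participant. Examples are admission to neonatal intensive care or "special care baby unit (yes/no"), respiratory support yes/no, the proportions given oxytocin and an epidural, mode of birth, and "Proportion of participants who had failed IOL (defined for the purposes of this study as caesarean section performed at < 4 cm"). Neonatal stay to hospital discharge is listed separately, among the hospital outcomes.

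The Statistical analysis section states one rule: "Continuous outcomes will be modelled using generalised linear models to estimate any changes in outcomes between the two interventions". Binary endpoints go to logistic regression. A p value of 0.05 counts as significant, secondary p values are not corrected, and missing data are not imputed. The article does not give a baby or woman without the event a value such as 0 h, and it does not label any of these measures descriptive.

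**The concern.** Randomisation makes the two arms comparable as wholes. It does not make comparable the subsets who later received oxytocin, had a caesarean or were admitted to a neonatal unit. If the induction method changes who enters a subset, a difference within it mixes any effect on the measure with a difference in who is being measured. Analysing women in their assigned arm does not remove this.

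The protocol gives reason to expect such differences. The systematic review of mechanical methods that it cites reports oxytocin use of 75% with balloon against 50% with prostaglandins, and its own primary hypothesis is fewer caesareans in the balloon arm.

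Neonatal unit stay matters most, because it bears on the secondary hypothesis of no increase in adverse events for the baby. Preventing brief admissions could appear as longer stays, and causing extra brief admissions could appear as shorter ones.

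**Working it through.** **1. The plan's own figure.** The inputs, from Sample size calculation, are p1 = 0.248, p2 = 0.188, two-sided alpha 0.05 and power 80%.

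n = [1.960·√(2·0.218·0.782) + 0.842·√(0.248·0.752 + 0.188·0.812)]² / 0.06² gives 743 per arm.

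With continuity correction, (n/4)·[1 + √(1 + 4/(n·0.06))]² gives 776 per arm, or 1552 in total. Both stated figures reproduce. The concern does not rest on them; 776 per arm is used only to size the subsets.

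**2. Expected subset sizes from the document's own rates.**

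- Oxytocin: 776 × 0.75 = 582 against 776 × 0.50 = 388.
- Caesarean, prostaglandin against balloon: 776 × 0.248 ≈ 192 against 776 × 0.188 ≈ 146.

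These show that the subsets are expected to differ in size. They do not show by how much, or in which direction, a conditional measure would be distorted.

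**3. Neonatal unit stay (assumed inputs; the documents give no admission rates or stay lengths).** In the control arm, 4% of babies stay 3 h and 6% stay 48 h. The intervention prevents half of the short stays and changes nothing else.

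| Measure | Control | Intervention |
|---|---|---|
| Admitted, of all babies | 10% | 8% |
| Mean hours, admitted only | (0.04·3 + 0.06·48)/0.10 = 30.0 | (0.02·3 + 0.06·48)/0.08 = 36.75 |
| Over 4 h, of admissions | 6/10 = 60% | 6/8 = 75% |
| Mean hours, all babies (0 if not admitted) | 3.00 | 2.94 |
| Over 4 h, of all babies | 6.0% | 6.0% |

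The range checked used short/long splits of 4/6%, 5/5% and 2/8%, with 25% to 75% of short stays prevented. Mean stay among the admitted always rose in the better arm, from 39.0 to 40.9 h at the least and from 25.5 to 39.0 h at the most. The share over 4 h among admissions rose by between 80% to 84% and 50% to 80%. Over all babies, the mean always fell slightly and the share over 4 h did not change. Swapping the arms turns the same arithmetic into an apparent benefit.

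**4. Dilation at caesarean (the protocol's 24.8% and 18.8%; the dilations are assumed).** Take early caesareans at 2 cm in 10% of control women and late ones at 7 cm in 14.8%.

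- Control: (0.10·2 + 0.148·7)/0.248 = 4.98 cm.
- If the 6 points avoided are all early: (0.04·2 + 0.148·7)/0.188 = 5.94 cm.
- If they are all late: (0.10·2 + 0.088·7)/0.188 = 4.34 cm.

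With early caesareans at 8% or 12% of control women, the mean moves from 5.39 to 6.47 or 4.87 cm, and from 4.58 to 5.40 or 3.81 cm. The same gain on the primary outcome therefore moves the conditional mean up or down. The failed-induction proportion, which uses all women, reads 10% to 4% in the first 10% case and 10% to 10% in the second. Both are interpretable.

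**The case against.** The strongest reply is that the analysis rule is a single general sentence that names none of these items. It cannot apply literally to everything listed, because the list also holds balloon-only items, the reason for caesarean and infant sex. The dilation entries may be meant as descriptors attached to a yes/no outcome; the median given for oxytocin points that way. The neonatal denominator is not written out either, and the 4 h item could be read as the proportion of babies admitted for longer than 4 h, which is the sound version. Since the unconditional partners would be reported alongside, a reader could see where an odd conditional mean came from. Stay among admitted babies also remains useful for planning services.

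Much of this stands, and it limits the point. A reader might infer that the protocol commits to a treatment-effect model for every conditional measure, that its intention-to-treat analysis is broken, or that a bias has been shown. The documents support none of these. The commitment follows only from a general rule without exemptions, analysis by assigned group is still what is stated, and the reversals rest on assumed inputs chosen to show the mechanism.

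What does not stand is that the matter is merely left to a later document. The caesarean condition is explicit, the clocks for unit stay and respiratory support run only in babies with the event, and the between-arm rule is stated without exception. Listing the partners does not make the conditional comparisons valid, and unit stay over 4 h among all babies is not clearly one of them.

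**Conclusion.** The point holds in limited form. Followed as written, the protocol would test between arms some measures defined only after a post-randomisation event, and those comparisons would not be randomised. For dilation at caesarean the restriction is explicit. For dilation at oxytocin start and epidural it follows from the definition. For neonatal unit hours, the 4 h proportion and respiratory-support hours it is the natural reading.

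The size of any bias cannot be given, because the documents hold no neonatal admission rates, stay lengths or dilation data. The illustrations show only that a conditional measure can move either way under a true benefit. The primary outcome, the 1552 sample size, the unconditional secondary outcomes and neonatal stay to hospital discharge are unaffected. The point is worth correcting because a misleading neonatal safety signal can be avoided at almost no cost.

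**What to change.** 1. Define neonatal unit stay over 4 h as a proportion of all randomised women's babies, so that a baby not admitted counts as no. Base the arm comparison on this and on the existing yes/no outcomes.
2. State in the Statistical analysis section that dilation at oxytocin start, epidural and caesarean, and unit stay and respiratory-support duration among babies with the event, are summarised by arm with the number contributing, without a treatment-effect model or p value.
3. Optionally, add unit hours and respiratory-support hours per baby, with zero if none, as a resource-use summary. Because most babies may contribute zero, this answers a different question from stay among the admitted and should not replace it.

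The cost is wording and one change of denominator; no new data are needed and the sample size does not change. The downside is that the conditional measures no longer carry a p value.

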**Fig. 1 Fig1:**
[figure not shown]
Schedule of enrolment, interventions, and assessments for the OBLIGE study

### Sample size calculation

At Auckland Hospital in 2015, the caesarean section rate in women who had undergone IOL (excluding women who had undergone previous caesarean section) was 24.8%, almost all of these women were induced using PGs [16]. In the small trial of outpatient vs inpatient balloon-catheter IOL, the risk of caesarean section rate decreased from 43 to 29% (a relative reduction of 32%) [11]. In order to detect a clinically meaningful change in risk of caesarean section rate from 24.8 to 18.8% (a relative risk reduction of 24%), with 80% power and a two-sided type 1 error of 0.05, we require a sample size of 743 women for each study group. Adding a continuity correction, the total sample size required is 1552 women.

### Recruitment

Potential participants are identified at the time of planning or booking an IOL, which can be between 1 day to 2 weeks prior to the IOL. Women are approached by a clinician or member of the research team to explain about the trial, encourage them to read the pamphlet or watch the video (both available at www.oblige.auckland.ac.nz), and answer questions. Inclusion and exclusion criteria are checked. Where possible, women’s interest in the trial is indicated in their paper-based or electronic medical records.

### Randomisation

On the day of IOL, after confirming eligibility, the clinician will obtain written consent from the participant. Participants will be randomised to one of two study groups, either the outpatient balloon-catheter group or the inpatient PG group, using a centralised, secure, online randomisation website. The randomisation schedule was prepared by the OBLIGE Trial Steering Committee (TSC). Randomisation is stratified by hospital and by parity (nulliparous or multiparous). Allocation is at a 1:1 ratio to outpatient balloon catheter: inpatient PG. The clinician, with support from the research team (if required), will perform the online randomisation, enrol the participant, and allocate the intervention to the participant.

### Blinding

Clinicians, who will be assessing the clinical outcomes, will not be blinded to treatment allocation; however, the outcomes are objective and most data are routinely collected during provision of clinical care. The researchers performing the data analysis, including the health economics analysis, will be blinded to group allocation.

### Data collection

Data will be collected using REDCap (https://www.project-redcap.org/), a secure web application for building and managing online surveys and databases. The data collection tool was developed and tested using an online, secure, central database specific to the OBLIGE trial. Researchers and clinicians involved in the trial receive their own user logon/password and undergo formal training to use the database.

The participant questionnaire (see Additional file 1) was developed for the purposes of this trial, and includes questions from the validated Childbirth Experience Questionnaire [17], questions recommended in the National Institute for Health and Care Excellence (NICE) guidelines on IOL [2], and questions from the patient satisfaction questionnaires from other recent maternity trials, provided on request to the PI (PINC – [name]; CLOSURE and GRoW – [name]). The staff satisfaction questionnaire (see Additional file 2) was derived from the OPRA outpatient IOL trial ([name]).

As allocation to either balloon-catheter or PG intervention will occur within 1 h of randomisation, the intervention will be complete within about 48 h, and then all women will give birth within the next 48 h, we expect participant retention to be straightforward. Moreover, we do not anticipate many participants to deviate from their allocated method of induction.

One data collection challenge will be the measurement of the secondary outcome of maternal satisfaction 4 weeks after the birth. The use of an electronic post-partum questionnaire by return of email was successful in a recent local clinical trial of decision aids for women birthing after previous caesarean section [18], with an 82% return rate. Researchers will follow up by phone if participants do not return their electronic questionnaire. After two reminders, and if 8 weeks has passed, then the case will be closed.

### Data management

Data will be collected manually on pre-printed data collection forms by clinicians at the time of clinical care provision, then entered into the REDCap study database retrospectively by the local research team. A member of the central research team will check and clean the entered data with the forms, and raise queries if data are missing or unclear. Once queries are resolved the data are locked.

### Statistical analysis

Baseline demographic and clinical characteristics will be described for each study group. Analyses will follow the principle of intention-to-treat; participants will be analysed according to the assigned intervention group at randomisation. Multivariable models will control for potentially confounding variables and include hospital site and parity. Binary endpoints will be analysed using logistic regression to estimate odds ratios for the intervention. Continuous outcomes will be modelled using generalised linear models to estimate any changes in outcomes between the two interventions. A *p* value of 0.05 will be considered as statistically significant. We recognise that there are a number of secondary outcomes; as they are secondary outcomes we will report *p* values without correction, which would be overly conservative. Missing data will not be imputed.

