There is low-quality evidence that outpatient care during the cervical ripening phase of IOL is an alternative to inpatient care. The Cochrane review included four RCTs comparing outpatient to inpatient labour induction [10]. Three used PGs; one used a balloon catheter. Sciscione et al. randomised 111 women to outpatient vs inpatient balloon catheter and found no differences between the groups in their primary outcome (change in Bishop score, a clinical assessment of cervical ripening) or secondary outcomes [11]. There were no adverse events or maternal morbidity in this small study. Women in the outpatient group spent 10 fewer hours in hospital. An unanticipated finding was the suggestion that fewer women in the outpatient group needed a caesarean section (29% vs 43%, RR 0.67 (95% CI 0.41–1.10)). The authors suggested that this may be attributed to clinician and patient perception of a longer IOL process in the inpatient group, which might have led to an earlier diagnosis of ‘failed induction’ in the inpatient group. The authors of this Cochrane review called for more trials examining IOL in outpatient settings to assess its safety and effectiveness.

There may be benefits for women to undergo balloon-catheter induction as an outpatient. Henry et al. randomised 101 women in an Australian tertiary hospital to outpatient balloon catheter vs inpatient PGs to assess feasibility, clinical effectiveness and acceptability [12]. Women randomised to outpatient balloon catheter were less likely to achieve vaginal birth within 12 h of admission (28% vs 53%, *p* = 0.01); however, they had comparable rates of caesarean section (34% vs 29%, *p* = 0.6). They spent 11 fewer hours in hospital, had less discomfort (26% reported feeling a lot of discomfort vs 58%, *p* = 0.03) and more hours of sleep (5.8 vs 3.4, *p* < 0.01), felt more able to relax (*p* = 0.01) and to rest (*p* = 0.01), and were more likely to choose this method of IOL again (65% vs 42%, *p* = 0.03). Two other trials in Canada and Australia also show women’s preference for, and satisfaction with, outpatient management [13, 14].

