### Characteristics of participants

The target population is pregnant women who develop one or more obstetric risks or complications where expedited birth by IOL is recommended by their clinician.

Women included in the study are pregnant women with a live singleton baby in a cephalic presentation; planning IOL at ≥ 37 weeks’ gestation, intact membranes, normal cardiotocography (CTG), Bishop score < 7, able to remain within 1 h of hospital and to have with them someone who can speak sufficient English to communicate with the hospital midwife on the telephone. A vaginal assessment of the cervix is required to establish the Bishop score, and a CTG also needs to be performed, in order to fully assess eligibility.

Women excluded from the study are women who have undergone previous caesarean; major fetal congenital anomaly; suspected fetal growth restriction; and maternal or fetal condition where the clinician feels that outpatient care would be contraindicated.

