#### Inpatient prostaglandins

The hospital clinician will place either a PGE2 gel (Prostin) or controlled-release pessary (Cervidil) in the vagina. Either method of administration is appropriate (hospital preference). The woman will be asked to rate her discomfort with PG placement on a NPRS of 0 (no pain) to 10 (worst possible pain). The woman does not need a routine CTG after placement, unless there is clinical concern, or to comply with local protocol. After 6 h (for gel) or 12–24 h (for pessary), the hospital midwife will perform a CTG, followed by an ARM. The woman will be asked to rate her discomfort with the ARM on a NPRS of 0 (no pain) to 10 (worst possible pain). If ARM is not feasible due to a low Bishop score, they will either place another PG or switch to second method. The Bishop score should be documented with each exam. Every PG should be prescribed on the National Medication Chart.

The assessment and administration of PG will be repeated regularly (not < 6 h for gel; not < 12 h for pessary) until ARM is possible, or the woman is established in labour or spontaneous rupture of membranes occurs, or the clinical team prefers to change to the second/alternative method, or to a maximum of six doses for gel or two doses for pessary. The timing and dose of each follow-up PG dose can be at the discretion of the clinical team. The date and time of the first and last PG will be documented. Whenever the woman starts to feel regular strong painful contractions, the midwife will perform a CTG. If ARM is still not possible, then the woman will be offered a balloon catheter (second method of cervical preparation) and remain an inpatient. However, if neither ARM nor balloon-catheter insertion is possible, then a senior clinician will decide how to proceed.

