### Primary outcome

Caesarean section:

the proportion of participants who give birth by caesarean section.

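### The primary model names hospital and parity but leaves all other adjustment to an open set of potential confounders; the Bishop score taken at eligibility is a sensible covariate to fix in advance

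*Protocol article*

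**What the plan says.** The primary outcome is binary: "the proportion of participants who give birth by caesarean section" (Primary outcome). For such endpoints the Statistical analysis section states: "Binary endpoints will be analysed using logistic regression to estimate odds ratios for the intervention". On adjustment it states: "Multivariable models will control for potentially confounding variables and include hospital site and parity". No other covariate is named there and no rule for choosing one is given.

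The Randomisation section names hospital and parity as the only strata, so the two named covariates match the design.

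On the Bishop score, the section Characteristics of participants says: "A vaginal assessment of the cervix is required to establish the Bishop score". The same section lists among the inclusion criteria: "intact membranes, normal cardiotocography (CTG), Bishop score < 7". The Literature review describes the outcome of an earlier small trial as "change in Bishop score, a clinical assessment of cervical ripening", which is the protocol's only account of what the score measures. The analysis section does not mention the score.

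**The concern.** Two things are loosely fixed.

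**The criterion.** In a randomised trial, baseline variables differ between the arms only by chance. Whether a variable might be a confounder is therefore not a useful test for including it. The useful test is whether it is expected to predict the outcome, judged before the data are seen. The wording gives no list and no such test, so more than one primary model would satisfy it.

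**The consequence for an odds ratio.** A logistic odds ratio is not collapsible: adding a prognostic covariate moves the target value even when the arms are perfectly balanced. An open covariate set therefore leaves the primary estimate partly undefined, and it leaves room for the model to be settled after data are available.

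The Bishop score is the obvious candidate to name. It has to be assessed before entry in every woman, it measures cervical readiness, and the entry rule leaves a wide spread of values. If it predicts caesarean section, omitting it gives up a little power for no saving.

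**Working it through.** **1. The plan's own figure.** Inputs from Sample size calculation: 24.8% vs 18.8%, two-sided alpha 0.05, power 80%, 1:1 allocation. With pooled p = (0.248 + 0.188)/2 = 0.218:

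n = [1.960 × √(2 × 0.218 × 0.782) + 0.8416 × √(0.248 × 0.752 + 0.188 × 0.812)]² / 0.060²

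= [1.1444 + 0.4901]² / 0.0036 = 742.2, rounded up to 743 per group.

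Continuity correction: (n/4) × [1 + √(1 + 4/(n × 0.060))]² = 185.5 × (2.0439)² ≈ 775.1, rounded up to 776 per group, or 1552 in total. Both stated figures reproduce, so no number in the plan is wrong.

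**2. Power gained by adding Bishop score.** The protocol gives neither the distribution of the score nor its association with caesarean section, so both are assumed and varied.

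*Setting A:* 1552 women, 24.8% vs 18.8%, parity already in the model. Half the women nulliparous, parity odds ratio 4, Bishop score with mean 3.5 and SD 1.5, limited to 0–6.

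| OR per Bishop point | Power without | Power with | Gain, 2000 trials | Gain, separate run of 4000 trials |
|---|---|---|---|---|
| 0.85 | 85.30% | 85.90% | 0.6 | 1.0 |
| 0.75 | 85.20% | 86.15% | 0.95 | 1.4 |
| 0.65 | 84.25% | 86.55% | 2.3 | 2.7 |

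In the 4000-trial run the paired standard error of the gain was 0.2 to 0.4 points. At an odds ratio of 1.0 there was neither gain nor loss. Type I error was near 5% with and without the score.

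*Setting B:* a wider spread (score uniform on 0–6), 776 per arm, site and parity not simulated, 2000 trials per row. Each power has a standard error of about 0.9 points.

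| OR per point | Control caesarean rate at score 0 / 6 | Power without | Power with | Gain | Mean treatment OR without / with |
|---|---|---|---|---|---|
| 1.0 | 24.8% / 24.8% | 81.95% | 81.80% | −0.15 | 0.701 / 0.701 |
| 0.9 | 30.9% / 19.2% | 81.85% | 82.15% | 0.30 | 0.701 / 0.699 |
| 0.8 | 38.0% / 13.8% | 83.20% | 84.10% | 0.90 | 0.700 / 0.692 |
| 0.7 | 45.9% / 9.1% | 81.05% | 84.30% | 3.25 | 0.703 / 0.682 |
| 0.6 | 54.4% / 5.3% | 82.30% | 87.95% | 5.65 | 0.701 / 0.662 |

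The last row requires a tenfold difference in caesarean rate across the entry range, so it is an outer bound. Type I error was 4.45% to 5.55% without the score and 4.45% to 5.80% with it (standard error about 0.5 points).

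**3. The target moves with the covariate set.** The unadjusted odds ratio implied by the design rates is (0.188/0.812)/(0.248/0.752) = 0.702. The last column of the Setting B table shows the same treatment effect expressed as 0.70 without the score and as low as 0.66 with it. Neither value is wrong; they are different quantities, and the plan does not say which is primary.

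**4. Exposure from an open set.** As an assumed worst case, take four optional prognostic covariates, fit all 16 subsets and report the smallest p-value (1000 trials, no treatment effect). Type I error was 6.6% with weak covariates (log odds ratio 0.2 per SD) and 9.2% with stronger ones (0.4 per SD), against 5.2% and 5.7% for one fixed model (standard error about 0.7 to 0.9 points). This bounds what the wording permits. It does not predict what the analysts will do.

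**The case against.** Much of the case on the other side is sound.

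- **A covariate list usually sits in the statistical analysis plan or the full protocol.** Neither is shown. It cannot be inferred that no list exists. What stands is that the published sentence gives a poor criterion and refers to no other document for the list.
- **The open phrase does not exclude the Bishop score.** That is correct; the score is unnamed, not ruled out.
- **A reader might infer that the protocol itself shows the entry score to govern the course of induction.** The tempting sentence is "If ARM is not feasible due to a low Bishop score, they will either place another PG or switch to second method". It describes reassessment after treatment, in the prostaglandin arm only. The balloon-catheter section makes further steps depend on whether the membranes can be ruptured, without mentioning the score. No passage links the baseline score to caesarean section. Its prognostic value is plausible from what it measures, and no more than that.
- **A reader might infer that failing to stratify on the score is a fault, or that omitting it biases the result.** Neither follows. Stratifying on hospital and parity alone is a legitimate choice, and chance imbalance is already covered by the type I error rate, as the simulations confirm.
- **A reader might infer that covariates will be picked by observed imbalance.** The text states no such rule. The Blinding section also keeps the analysts unaware of allocation, which limits steering towards a favoured arm. It does not remove the exposure in step 4, because that calculation takes the smallest two-sided p-value in either direction and needs no knowledge of which arm is which.
- **Adding a covariate is not automatically free.** The protocol requires a score to establish eligibility but does not say that its numeric value is held in the database for every woman. The analysis section rules out imputation, so a missing value could drop a woman from the primary model. This stands, and the fix has to deal with it.

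**Conclusion.** The point holds in a limited form. The adjustment rule fixes hospital and parity and leaves the rest open, on a criterion that suits observational data better than a randomised comparison, for an effect measure that depends on the answer. That is the main defect.

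The Bishop score is a secondary, constructive part: a plausible prognostic covariate, assessed before randomisation, that could be named. Not naming it costs about 0 to 3 percentage points of power for odds ratios per point from 1.0 to 0.65 in Setting A, and would reach about 6 points only under the extreme assumptions of Setting B. These sizes rest wholly on the assumed distribution and association. Without the score, simulated power was at or above 81% in every case, so the planned 80% is not threatened and 1552 stands. This is a minor improvement, not an error that endangers the trial.

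**What to change.** Before unblinding, replace the open phrase with one primary model for caesarean section: allocated arm, hospital, parity and the Bishop score recorded at eligibility, in a prespecified form (for example a single linear term). State that any other covariates enter sensitivity analyses only.

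Add a simple prespecified rule that keeps a woman with no numeric score in the primary analysis, for example a missing-value category or one fill-in value set without regard to arm or outcome. Say that the statement against imputation does not apply to this baseline covariate. If an analysis plan already lists covariates, align the two texts.

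The cost is two or three sentences, with no extra visits or measurements. One check is needed: that the eligibility score is stored as a number. The timing is favourable: the article reports just over 450 of 1552 women recruited and no interim analysis planned, so the model can be settled without sight of outcomes by arm.
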